#### Informed consent

The online participant information and consent form contain extensive details about the research project such as information regarding interventions, assessment, research procedures, potential risks, reimbursement, confidentiality, and freedom to withdraw from participation. Once interested, individuals will provide informed consent via a web-based survey form, and they will then be booked in for telephone screening call.

#### Telephone screening

The telephone screening will take about 30 minutes and will cover: DSISD [77], medication use, engagement with psychotherapy or sleep treatments, and a risk assessment. Individuals who meet exclusion criteria due to the presence of other sleep disorders will be encouraged to discuss their conditions with a health professional, with appropriate referrals being made whenever necessary. Individuals eligible for the study will be booked in for a study information session and are sent the baseline questionnaire.

#### Randomization and blinding

Eligible participants will be randomized using permuted block randomization generated in advance. Block designs with varying block sizes of 4, 6, and 8 are used. Random seeds are generated to assure allocation concealment and pre-guessing of the allocation sequence at the end of each block. Randomization is stratified by baseline ISI (≤14 and ≥15). The randomization scheme is generated and set up in research electronic data capture (REDCap) by a member of the research team ([name]) who is (1) not involved in the recruitment or delivery of the study intervention and (2) is not one of the principal investigators. REDCap (hosted at Monash University) [78] is a secure, web-based application designed to support data capture for research studies, with audit trails for tracking data manipulation and automated export procedures for data downloads. To randomize a participant, an authorized researcher will log into REDCap, enter eligibility and stratification data on the participant, and receive the group allocation. Follow-up study measures will be either self-completed or conducted by research staff who are blinded to the condition. Participants will not be blinded but asked to withhold group allocation from research staff during the follow-up study measures. The initial screening telephone interview will be carried out by a provisional psychologist ([name]) under the supervision of a clinical psychologist (BB).

#### Timing of assessments and intervention

Participants undertake online questionnaires administered via REDCap at two-time points: baseline (Baseline) and post intervention (Post). Figure 1 below contains a timeline of assessments and intervention material. All online questionnaires and telephone calls will be delivered by the research team in English.

**Figure 1. F1:**
[figure not shown]
Novel inomnia treatment experiment (NITE) study flowchart.

All participants will attend two meetings (in-person or videoconferencing) with a researcher at baseline. The first meeting (~30 minutes) will cover study orientation and instruction regarding the research equipment. Following this, participants will complete the second meeting (~60 minutes for intervention, ~30 minutes for control; see details in the intervention condition section).

Participants also received four scheduled phone calls: (1) the aforementioned screening call, (2) two check-in calls 1 and 4 weeks after baseline (~10 minutes each) to encourage adherence and troubleshooting, and (3) a final telephone call will be made by a researcher blinded to group allocation at post-intervention to administer the DSISD Insomnia module (~10 minutes).

All telephone communication and videoconferencing sessions will be audio recorded with consent. Audio recordings are used for assessing reliability and intervention fidelity and are stored securely with password protection.

Participants will receive reminder emails to prompt questionnaire completion. Following the final assessment and the return of research equipment, participants will be sent up to a 70 AUD gift voucher as a token of appreciation for participating. The gift card amount is calculated based on the use of Fitbit and the completion of the sleep diaries. If participants use Fitbit for seven nights and complete the sleep diary for 5 nights per week, they will receive 10 AUD (up to 50 AUD for 5 weeks of participation). All participants will receive 20 AUD for completing online questionnaires.

#### Adverse events

Adverse effects will be monitored during each participant contact throughout the research project during the check-in phone calls, and via post-intervention questionnaire. Participants will also be instructed to contact the research team immediately if they experience unwanted adverse effects during participation so that intervention may be appropriately adapted (e.g. not using Dreem headband). Severe adverse events will be included in human research ethics reports.

#### Risk

A risk assessment will be undertaken during the initial screening telephone interview. It will assess suicidal/homicidal ideation, plan, history of injurious behavior, and engagement with mental health care. Participants deemed to be at high risk, defined as current suicidal/homicidal ideation with plan and/or history of harm will be excluded from the study and referred to relevant services for clinical care. Participants at medium risk, defined as experiencing current ideation to harm self/others but have no plan or previous history of harm, will be included if no other exclusion criteria are met; they are provided referral options for mental health care. Participants at low risk will be included if no other exclusion criteria are met.

#### Intervention conditions

Both interventions will include an individual session and two check-in calls. Interventions will be manualized to ensure consistency. A provisional psychologist undertaking doctoral training in clinical psychology ([name]) will be trained in the intervention, and competence in delivering the content will be assessed prior to study commencement by a clinical psychologist (BB). The provisional psychologist will receive regular supervision throughout the study. Participants in each group will be offered the content the other group received following the completion of the study.

#### Intervention condition

Participants in the intervention condition will receive the following components combined:

1 An individual session conducted by a provisional psychologist ([name]) that covers: (a) the differences between sleep variables measured using self-report and sleep measured using wearables, (b) the nature of sleep–wake state discrepancy and its relevance to insomnia, and (c) healthy interpretation of sleep–wake state discrepancy, through an assisted interpretation of participants' baseline sleep data (measured via Fitbit, Dreem, and self-report). Although the session draws upon strategies commonly used in CBT-I (e.g. addressing thoughts and beliefs related to sleep–wake state discrepancy), it will not include key components of CBT-I (e.g. stimulus control, sleep restriction).2 Access to daily Fitbit sleep data through the Fitbit app, including TST, sleep start time, and wake time.3 An illustrated weekly report (see Supplementary Material) that compares self-report (i.e. sleep diary) and objective (i.e. Fitbit and Dreem) sleep data. This report will be emailed to participants each week throughout participation and will include both daily and weekly summaries of: (a) TST (sleep diary and Fitbit), (b) SE (sleep diary and Fitbit), (c) SOL (sleep diary and Dreem), (d) wake after sleep onset (sleep diary and Dreem), and (e) sleep stages (Dreem). Data from two sources will be plotted together (e.g. sleep diary and Fitbit TST), and these figures will be accompanied by interpretations of discrepancies and information on how to use this information for managing concerns about sleep. These reports will be automatically generated weekly using an R-script that fetches data from Fitbit and Dreem servers via application programming interface (API).

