Therefore, this randomized controlled study utilizes two conditions: one condition provides feedback on wearable measured sleep variables and discusses sleep–wake state discrepancy, and the other (control) condition provides information about sleep hygiene. This study aims to: (1) Examine whether providing individuals with insomnia feedback about sleep using sleep wearable devices, along with support for interpretation of sleep–wake state discrepancy improves symptoms of insomnia as the primary outcome. It is hypothesized that providing monitoring and feedback will result in a significantly greater reduction in insomnia symptom severity from baseline to post-intervention compared to control. Group differences in the changes of sleep and mental health domains (e.g. symptoms of depression, anxiety, and sleep-related daytime functioning) are also explored given their potential associations with both sleep perception and insomnia symptoms [4, 69–73], and (2) Explore potential mechanisms of change, including sleep–wake state discrepancy (operationalized as the differences between self-report and wearable measured sleep variables), dysfunctional beliefs and attitudes about sleep, presleep arousal, and aspects of sleep architecture (e.g. increased percentage spent in non-rapid eye movement [NREM] and rapid eye movement [REM], reduction of NREM and REM fragmentation, and increase slow wave density and amplitude).

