#### Control condition

This control condition is designed to control for nonspecific factors such as receiving sleep information and time with a researcher. The control condition will be instructed to use the study devices (i.e. Fitbit and Dreem), however, they will not receive feedback about their objectively recorded sleep throughout their participation in this study. They will be able to utilize the Fitbit app for non-study related purposes (e.g. exercise, step tracking) but the sleep information tile will be hidden. They will receive their weekly sleep reports (see Supplementary Material) at the end of the study, following the completion of the final assessment. The control condition will receive a sleep education session conducted by the provisional psychologist ([name]) covering: (1) psychoeducation about sleep (e.g. information about what the functions of sleep, sleep cycles, sleep stages, the homeostatic sleep drive, and circadian rhythms), and (2) sleep hygiene (e.g. healthy sleep habits regarding light, body temperature, physical activity, noise, food, caffeine, alcohol, and bedding). Participants will not be instructed to alter any sleep-related behaviors.

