### Measures

#### Daily sleep measures

The daily sleep diary that will be utilized in this study to assess self-reported sleep behaviors is adapted from the consensus sleep diary [79]. Participants will be asked to complete the sleep diary each day (~2 minutes per day; via computer or phone app) as soon as they have woken up, for the duration of the research project. The sleep diary collects information about experiences over the previous day and night (e.g. sleep timing, number of nighttime awakenings, naps, caffeine consumption, and medication for sleep). The consensus sleep diary has shown good clinical utility, usability, and ability to discriminate people with sleep dysfunction from normal sleepers [80].

Participants will be instructed to wear a Fitbit Alta HR (Fitbit Inc., 2017 release) on their non-dominant hands for the duration of the research project. The Fitbit Alta HR has been found to provide equivalent estimates to research-grade actigraphy for gross sleep parameters (e.g., total sleep time, sleep efficiency) in and outside of the laboratory [66, 81]. However, the Fitbit sleep staging is limited in accuracy compared to PSG [81–83], and is not used in this study.

Participants will be given an optional Dreem headband (Dreem Inc., version 2) to wear on their heads while sleeping for the duration of the research project. Compared to PSG, Dreem had high concordance for raw signal detection with 83.5% accuracy for overall scoring across five stages (i.e. all sleep stages and wake) and 74.0% accuracy with wake epochs alone (i.e. specificity) [84].

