#### Statistical and power analysis

All analyses will be conducted on an intention-to-treat basis. Missing data is expected in this study design as participation occurs over several weeks and will be addressed using multiple imputations through chained equations. Pooled results from the multiply imputed data will be the primary analyses. Analysis will be conducted in R.

To examine group differences in primary and secondary outcomes, each outcome will be entered into a separate multiple regression model. Each outcome at post-intervention will be the dependent variable, with the outcome at baseline included as a covariate. Treatment conditions will be dummy coded and entered as the focal predictor. Stratification factors will be dummy coded and included as covariates in all models.

Each outcome will be evaluated for assumptions. If an outcome demonstrates substantial skew or non-normality, transformations (e.g. log, square root) will be evaluated to see if they improve normality. If outliers and extreme values are present, sensitivity analyses will use quantile regression to estimate the medians rather than linear regression as quantile regression models are less sensitive to extreme values. Scatter plots will be used to evaluate the association between each outcome at baseline and post-intervention. If there is evidence of substantial non-linearity, a generalized additive model will be used with a smooth term on the baseline outcome to allow non-linear associations.

In all cases, effect sizes will be calculated to quantify the size of group differences, 95% confidence intervals calculated around estimates of treatment group differences, and within-group change scores summarized to quantify the average change over time in each group. Sensitivity analyses will be conducted using only participants with complete data on each outcome. To explore predictors of treatment response, potential predictors will be incorporated in regression analyses as predictors or moderators.

Assuming an attribution rate of 20%, randomizing 90 participants in total (45 per group) will give the study 80% power (two-tailed *a* = 0.05, regression analyses) to detect a medium effect size (*d* = 0.6) on the ISI as the primary outcome. The effect size estimation is based on a previous behavioral intervention experiment, also included the ISI as the outcome, and addressed the discrepancy in self-report versus objective sleep information in individuals with insomnia [45].

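### Only the intervention arm can see Fitbit sleep values before completing the diary, so the exploratory diary-versus-Fitbit discrepancy can shrink in that arm without any change in perception

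*Protocol article*

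**What the plan says.** The Introduction sets as the second aim to "Explore potential mechanisms of change, including sleep–wake state discrepancy", "operationalized as the differences between self-report and wearable measured sleep variables". Dysfunctional beliefs, presleep arousal and sleep architecture are listed beside it.

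The Intervention condition section gives that arm "Access to daily Fitbit sleep data through the Fitbit app, including TST, sleep start time, and wake time". It adds a weekly emailed report that plots diary against Fitbit for total sleep time (TST) and sleep efficiency (SE), and diary against Dreem for sleep onset latency (SOL) and wake after sleep onset (WASO).

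The Control condition section has controls wear the same devices, but "they will not receive feedback about their objectively recorded sleep throughout their participation in this study". They may use the Fitbit app for other purposes, but "the sleep information tile will be hidden". Their weekly reports come after the final assessment.

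Under Daily sleep measures, "Participants will be asked to complete the sleep diary each day", on waking, by computer or phone, throughout the project. The diary covers sleep timing among other items. The article does not state the order of diary and app, a delay in app access, or a feedback-free period for measuring discrepancy.

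**The concern.** A discrepancy score measures perception only if the self-report is made independently of the device. In the control arm the device value is hidden, so that condition is met. In the intervention arm the value is available every day, possibly on the same phone as the diary. A participant who looks first can copy it or lean towards it.

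That moves the discrepancy towards zero in one arm only. Randomization does not remove the effect, because exposure to the device value is part of the allocated condition. A smaller discrepancy in the intervention arm could then mean a corrected perception or a transcribed number, and the data would not separate the two. What is at stake is the interpretation of one exploratory mechanism. The order of diary and app also cannot be imposed once the data are collected.

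**Working it through.** **Setting the sections side by side**

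1. Discrepancy is self-report against wearable (Introduction), so the diary supplies half of the variable.
2. The values named as visible in the app are TST, sleep start time and wake time (Intervention condition). TST is one of the two quantities that the study's report pairs with Fitbit. The other, SE, depends partly on TST and is exposed in part.
3. SOL and WASO are paired with Dreem and described as fed back in the weekly report. Same-night copying is not shown for them.
4. Controls do not see their sleep values during the study (Control condition).
5. The diary instruction sets a time, on waking, but not an order relative to the app (Daily sleep measures).

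**Scale**

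The plan has no figure of its own to reproduce. It gives no mean or SD for discrepancy and no rate of copying. The inputs are:

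- D, the mean discrepancy: 30 or 60 minutes (assumed).
- c, the share of intervention-arm nights copied: 10%, 25% or 50% (assumed). It can also be read as the average fraction of the gap closed by anchoring.
- SD: 45 to 60 minutes (assumed).
- Completers per arm: 45 × (1 − 0.20) = 36, from the 45 per group and 20% attrition in Statistical and power analysis.
- Two-sided alpha of 0.05, from the same section.

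With perception unchanged, the observed mean in the intervention arm is (1 − c) × D, against D in the control arm. The false difference is c × D, and its standardized size is d = c × D / SD. The chance of a significant result favouring the mechanism is Φ(d / √(2/36) − 1.96).

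Example: D = 60, c = 0.50, SD = 60 gives a 30-minute difference and d = 0.50. Then 0.50 / 0.2357 = 2.12, 2.12 − 1.96 = 0.16, and Φ(0.16) = 56%.

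| D (min) | c | False difference (min) | d (SD 60 to 45) | Chance of p < 0.05 |
|---|---|---|---|---|
| 30 | 10% | 3 | 0.05–0.07 | 4–5% |
| 30 | 25% | 7.5 | 0.125–0.17 | 8–11% |
| 30 | 50% | 15 | 0.25–0.33 | 18–29% |
| 60 | 10% | 6 | 0.10–0.13 | 6–8% |
| 60 | 25% | 15 | 0.25–0.33 | 18–29% |
| 60 | 50% | 30 | 0.50–0.67 | 56–81% |

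With no artefact, the last column would be 2.5%, since it counts one direction of a two-sided 5% test. The artefact is small at 10% copying and becomes material only when copying is common and the discrepancy is large.

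**The case against.** The strongest reply is that the diary is already due on waking in both arms, that finer wording belongs in participant instructions or the manual, and that a journal article may leave it out. The waking rule does reduce the opportunity, and the full protocol may contain an order. But a time is not an order when both tools can be on one phone. The voucher terms reward diary completion and state no timeliness condition. The article describes the diary instruction and the device access in some detail and leaves this gap between them.

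A second reply is that showing the data is the intervention, so later estimates informed by earlier feedback may be the intended recalibration. That stands. Putting the diary first removes only same-night copying. It cannot separate recalibration from anchoring on previous nights.

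The Introduction also notes that some people overestimate their sleep. D in the calculation is the mean net of both directions, so a mixed sample would have a smaller D and a smaller mean shift.

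A reader might infer several stronger points that the documents do not support:

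- *The whole second aim is compromised.* The other listed mechanisms are not diary-minus-device scores, and the Dreem pairings are not shown to be open to same-night copying.
- *The plan would credit discrepancy as the cause of any gain on the Insomnia Severity Index.* No section contains such a rule.
- *The plan tests moderation where it needs mediation.* The words "potential predictors will be incorporated in regression analyses as predictors or moderators" concern predictors of treatment response and are not offered as the mechanism analysis. The model for an exploratory aim may properly be left to the full protocol or SAP.
- *The mechanism variable should be defined by app sync times, or the EEG analyses limited by when participants opted for the headband.* The documents do not say that app viewing is recorded, and syncing is not viewing. Selecting nights by sync order conditions on behaviour after randomization. The optional headband is a separate matter with no bearing on diary copying.

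**Conclusion.** The point holds in a bounded form. As the article is written, diary TST and sleep timing, and partly SE, can be anchored on the Fitbit value in the intervention arm only. This can shrink the measured discrepancy with no change in perception, in the direction that favours the proposed mechanism.

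It concerns an exploratory variable. The primary outcome does not use the diary and is not directly affected. The size cannot be stated from the documents. The range of 3 to 30 minutes rests wholly on the assumed discrepancies and copying rates above, and the chances of a false positive rest in addition on the assumed SD. The case for acting is that the bias differs by arm, has a known direction and is cheap to prevent, not that it is shown to be large.

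**What to change.** In Daily sleep measures, instruct both arms to submit each day's diary before opening any sleep app or sleep report. This leaves the intervention intact, because participants still see all their data afterwards.

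Where diary submission times are recorded, add a sensitivity analysis of the discrepancy limited to diaries submitted promptly on waking. State two limits with it: the selection is made on behaviour after randomization and so may itself differ by arm, and residual anchoring from earlier feedback remains.

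The cost is one extra instruction to participants, and a few diary nights dropped from the sensitivity analysis.

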#### Control condition

This control condition is designed to control for nonspecific factors such as receiving sleep information and time with a researcher. The control condition will be instructed to use the study devices (i.e. Fitbit and Dreem), however, they will not receive feedback about their objectively recorded sleep throughout their participation in this study. They will be able to utilize the Fitbit app for non-study related purposes (e.g. exercise, step tracking) but the sleep information tile will be hidden. They will receive their weekly sleep reports (see Supplementary Material) at the end of the study, following the completion of the final assessment. The control condition will receive a sleep education session conducted by the provisional psychologist ([name]) covering: (1) psychoeducation about sleep (e.g. information about what the functions of sleep, sleep cycles, sleep stages, the homeostatic sleep drive, and circadian rhythms), and (2) sleep hygiene (e.g. healthy sleep habits regarding light, body temperature, physical activity, noise, food, caffeine, alcohol, and bedding). Participants will not be instructed to alter any sleep-related behaviors.

